## **Guidelines for adverse events' possible relationship to treatment:**

1. Not related – no temporal relationship, other aetiologies are very likely the cause
2. Possibly related – less clear correlation, other aetiologies are also possible
3. Probably related – clear temporal correlation with improvement on discontinuation of medication, and not reasonably explained by the patient's known clinical condition.
4. Related – clear temporal relationship with repeated treatment test or clinical assessment.

Study participants with adverse events will be monitored with appropriate clinical assessments and laboratory tests according to the decision of the attending doctor. All adverse events will be followed until satisfactory recovery or stabilization.

A serious adverse event (SAE) is understood to be any incident involving a significant risk of the death or disability of the study participants (or their offspring), including, but not limited to, an event that results in:

- death
- life-threatening episodes – in the investigator's opinion the study participant was in immediate risk of death from the adverse event when it appeared
- requires hospitalization or prolongs existing hospitalization
- is permanently disabling

- is a congenital anomaly

## **Grading of adverse events:**

The medical investigator should attempt to identify all clinical and objective reactions from the study participants in the treatment and determine their relationship with the study procedure. Reactions, if there are any, should be graded according to the following scale:

1 = slight

2 = moderate

3 = severe

4 = life-threatening

## **Reporting of adverse (AE) and serious adverse effects of (SAEs)**

The investigator is responsible for ensuring that all adverse events are recorded in the participant’s Case Report Form.

The sponsor is responsible for ongoing monitoring of the study's risk/benefit relation. If there arise or are seen to be situations that may affect the safety of the study participants or the performance of the study, these must **always** be immediately reported to all investigators involved with the study, as well as the relevant Research Ethic Comities.

The sponsor shall at all-time be kept informed by the investigator of any adverse events. At the end of the trial, the final report shall contain a description of all side effects.

Serious adverse events – SAEs - should be reported immediately by the investigator to the sponsor (sponsor-investigator). SAEs must be reported annually by the Investigator to the Research Ethics Committee throughout the whole trial period, together with a report on the safety of the study participants.

# **Statistical analyses**

## **Sample size estimation**

The estimation of the number participants, experimental days and number of observers will be based on simulations performed with selected relevant scenarios for the desired precision of the involved variance components. The simulations will be based on raw data obtained from a previous study (2). Even though the ratio between the intra-individual variance and the inter-individual variance in secondary hyperalgesia may exceed 25% we aim to include a slightly higher number of participants and implement a larger number of study days in order to investigate the reproducibility the area of secondary hyperalgesia.

The simulations will include scenarios with up to 10% missing data in a missing at random (MAR) scenario, where the risk of missingness is increased on the second experimental day in study participants who have large areas of secondary hyperalgesia on the first experimental day.

## **Plan of statistical analysis**

To determine the variance of the areas of secondary hyperalgesia derived respectively from the study participant, the experimental day and the observer, a variance component model will be employed, to investigate which of these three types of variance is the most influential of the total variance.

’Limits of agreements’ plot for agreement between areas of secondary hyperalgesia on different experimental days and different observers will be developed and evaluated in accordance with the relevant measures of reproducibility. For each of the secondary outcomes, the ability of PCS, HADS, HPDT, Max-VAS and VAS-AUC (following LTS), to predict individual variations in areas of secondary hyperalgesia will be investigated by linear regression. Significance of the predictors will be assessed by Analysis of variance (ANOVA) methods and their predictive abilities will be quantified by various summaries of prediction errors including 95% prediction intervals for the predictions

For all analyses, an intention-to-test analysis will be performed including all subjects who participated in the first experimental day. Analyses will be based on all observed data. If missingness exceeds 5% and there is indication of violation of “missing completely at random” (MCAR) a sensitivity analysis based on an appropriate model for missingness at random (MAR) or not at random (MNAR) will be performed.

A family wise error rate of 0.05 will be used and simultaneous assessment of multiple p-values will be subjected to single-step adjustment

#

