# **Aim**

The aim with this prospective, observational and descriptive study is to validate previous results from retrospective investigations that indicate that secondary hyperalgesia is a robust and reproducible phenomenon, with a low intra-individual and a high inter-individual variability. Moreover, we aim to validate that the degree of secondary hyperalgesia can be applied as a phenotypic phenomenon and a biomarker for the excitability of the central nervous system. Lastly we aim to investigate if the area of secondary hyperalgesia can be associated with the individual psychological vulnerability in the study participants.

In a prospective cohort of 50 healthy volunteers we aim to:

1. Investigate the size of the area of secondary hyperalgesia following brief thermal sensitization on four different study days.
2. Investigate heat pain detection thresholds and pain during 1 min. thermal stimulation of the skin.
3. Determine the psychological vulnerability evaluated by the Hospital Anxiety and Depression Scale and the Pain Catastrophizing Scale.

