# **Outcomes**

**Primary outcome**

To determine the intra- and inter-individual variance, and the inter- and intra-observer variance of the secondary hyperalgesia areas following brief thermal sensitization on 4 separate experimental days with two different observers.

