# **METHODOLOGY**

## **General procedure**

On the study days all study participants will be tested lying in the supine position. The study will be conducted in a quiet secluded room, where only the study participant and the investigator will be present.

The study participants will be tested with 3 types of pain conditioning on four separate study days. The 3 types of pain conditioning consist of Brief Thermal Sensitisation (BTS), Heat Pain Detection

Threshold (HPDT), and Long Thermal Stimulation (LTS), (see Clinical evaluations). HPDT and LTS are conducted subsequent to BTS. , the order of the stimulations (HPDT and LTS) is randomised for each patient and each experimental day, by a randomisation schedule developed by Copenhagen Trial Unit. Likewise, the investigators/observers responsible for testing and data registration will also be randomised, so the same investigator will not be responsible for 2 consecutive experimental days. There will be 2 different investigators responsible for the testing. The randomisation schedule is stored in sealed and opaque envelopes to secure adequate allocation concealment

The study participants will be tested with three types of pain conditioning on four separate experimental days. Furthermore, the study participants will complete the two psychological tests, PCS and HADS (see Assessments and tests)

The study participants will be tested with the following types of pain conditioning:

1. Brief Thermal Sensitisation (BTS). The test is conducted centrally on the anterior part of the right thigh. BTS will be conducted at the time: 0 min. (see Assessments and tests).
2. Heat pain detection threshold (HPDT). The test is conducted centrally on the anterior part of the dominant lower arm. HPDT (see Assessments and tests) will be conducted at the time: 7 or 10 min. depending on the randomisation (see Randomisation).
3. Long thermal stimulation (LTS). The test is conducted centrally on the anterior part of the non-dominant lower arm. A continuous VAS-measurement will be performed during the test. The test will be conducted at the time: 7 or 10 min. depending on the randomisation (see Randomisation).

The entire study consists of one screening day and four identical study days. The screening and study days will proceed as follows:

Screening day:

- Oral information regarding the project is delivered by the primary investigator. The participant will be given time to consider the information.

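### The three-source variance partition has no stated place for participant-specific disagreement between the two observers, so the observer share may be understated

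*Protocol*

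**What the plan says.** The primary outcome is "To determine the intra- and inter-individual variance, and the inter- and intra-observer variance of the secondary hyperalgesia areas" over four experimental days (Protocol, Primary outcome). For the analysis, the Plan of statistical analysis introduces its model with the words "To determine the variance of the areas of secondary hyperalgesia derived respectively from the study participant, the experimental day and the observer, a variance component"; the purpose given is "to investigate which of these three types of variance is the most influential of the total variance". It does not say whether observer is crossed with participant or nested in it, and it names neither a residual nor an interaction. The same section also plans limits-of-agreement plots between days and between observers.

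The design comes from General procedure: "The entire study consists of one screening day and four identical study days", and observers are randomised "so the same investigator will not be responsible for 2 consecutive experimental days. There will be 2 different investigators responsible for the testing". The cohort is 50 volunteers (Aim).

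**The concern.** Two observers, four days and no observer on consecutive days leave only the sequences ABAB and BABA. Each complete participant therefore has two areas mapped by each observer, and areas may be correlated within an observer–participant pair. Such correlation is plausible. The border is mapped by hand from the participant's report (Assessment of secondary hyperalgesia), and the blinding described under Study Design covers only the psychological tests. An observer could therefore be influenced by an earlier mapping of the same person.

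In a crossed three-source model, the observer term holds only a shift common to all participants. If one observer maps larger areas in some people and smaller ones in others, that disagreement is inter-observer variance in substance, but it is booked elsewhere. At stake are the inter-observer and intra-observer estimates, both primary, and the ranking that the plan sets out to make.

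**Working it through.** **Inputs from the Protocol:** 50 participants (Aim); four study days, two observers, strict alternation (General procedure). The Sample size estimation section says the intra/inter-individual variance ratio may exceed 25%; 0.25 is used here only as an anchor. The Protocol states no variance components, so there is no figure of its own to reproduce.

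**Assumed:** participant variance Vp = 1, same-observer residual Ve = 0.25, observer shift variance Vo = 0.05, participant-by-observer variance Vpo from 0 to 0.30. Complete data.

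**Degrees of freedom.** There are 50 × 4 = 200 areas. With participant, day and observer fitted, the residual has 200 − 1 − 49 − 3 − 1 = 146 df. These split into 48 for participant-by-observer and 98 for replicate error. Without day in the model the split would be 49 and 100. The observer shift itself has 1 df.

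**Expected mean squares:**
- participant: Ve + 2Vpo + 4Vp
- observer: Ve + 2Vpo + 100Vo
- participant-by-observer (48 df): Ve + 2Vpo
- replicate (98 df): Ve

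**Three-source model.** The last two lines are pooled:
- residual = Ve + (48 × 2 / 146)Vpo = Ve + 0.6575Vpo
- participant = Vp + [(2 − 0.6575)/4]Vpo = Vp + 0.3356Vpo
- observer = Vo + [(2 − 0.6575)/100]Vpo = Vo + 0.0134Vpo

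An exact quadratic-form calculation for this design gave the same three weights, and about zero for day.

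**Results.** Total variance = 1 + 0.25 + 0.05 + Vpo. The true observer-related share is (0.05 + Vpo)/total.

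| Vpo | True observer-related share | Share reported | Participant reported (true 1) | Residual reported (true 0.25) |
|---|---|---|---|---|
| 0 | 3.8% | 3.8% | 1.00 | 0.25 |
| 0.05 | 7.4% | 3.8% | 1.02 | 0.28 |
| 0.10 | 10.7% | 3.7% | 1.03 | 0.32 |
| 0.20 | 16.7% | 3.5% | 1.07 | 0.38 |
| 0.30 | 21.9% | 3.4% | 1.10 | 0.45 |

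At Vpo = 0.20, for example: true 0.25/1.50 = 16.7%; reported (0.05 + 0.0134 × 0.20)/1.50 = 3.5%.

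**Simulation check.** In 150 data sets with Vp = 1, Vpo = 0.20 and Ve = 0.25, fitted by REML with day and observer fixed, the model without the term averaged 1.05 (participant) and 0.38 (residual). With the term it averaged 0.98, 0.20 (participant-by-observer) and 0.25.

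**Ranking.** If day-to-day variation is read as the residual, then at Vpo = 0.30 the observer-related variance (0.35) exceeds it (0.25). The three-source model reports 0.05 against 0.45, the opposite order.

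**Intra/inter ratio.** At Vpo = 0.20 the model reports 0.38/1.07 = 0.36. If intra-individual means same-observer, between-day variance, the true ratio is 0.25 and the reported one is too high. If it includes observer disagreement, the true ratio is (0.25 + 0.20)/1 = 0.45 and the reported one is too low.

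**The case against.** The strongest objection is that the sentence lists sources and is not a model formula. It names no residual and excludes no interaction, and exact random-effects terms are commonly left to a statistical analysis plan. If observer is meant as nested in participant, the disagreement stays in the observer component and nothing is lost. This stands in part: the Protocol does not rule the term out, and a reader who infers that it does goes beyond the text. But the section fixes a three-way partition and a ranking of exactly those three sources, and it does not state nesting.

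Second, the size is unknown and may be zero. That stands. The shift in the participant component is also small beside its sampling error: 0.07 at Vpo = 0.20, against a simulated standard deviation of about 0.22.

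Third, the planned between-observer limits of agreement would partly show the problem. At Vpo = 0.20 their half-width is 1.96 × √(2 × 0.45) = 1.86 between observers, against 1.96 × √(2 × 0.25) = 1.39 within an observer, both across different days. That helps, but it does not correct the components or their ranking.

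Two stronger readings are tempting. A reader might infer that a test of the observer shift would reject too often. The Protocol plans no such test; it mentions significance for the predictors in the secondary outcomes, so an error rate for an observer test is not a finding here. A reader might also infer that every shift favours the study's expectation of little variation within a person and much between persons. That fails: the participant component is inflated, but same-observer day-to-day variance is overstated too, and the direction of the ratio depends on the definition used.

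**Conclusion.** The concern holds conditionally. Under the crossed reading, any participant-by-observer variance goes about 34% to participant, 66% to the residual and about 1% to observer. The observer share is then understated, and both the participant component and the same-observer day-to-day variance are overstated. Under the stated assumptions with Vpo = 0.20, the observer-related share reads about 3.5% instead of 16.7%; with Vpo = 0 there is no bias.

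The participant is the largest source in every scenario shown and probably remains so. What can change is the inter-observer estimate and the ranking of observer against day. The split rests on complete, balanced data; the percentages rest on assumed variances. This is an inexpensive improvement to the primary analysis, not a fault that invalidates it.

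**What to change.** In the Plan of statistical analysis, state how observer relates to participant and add a participant-by-observer random component (equivalently, observer nested in participant plus an overall observer shift). Report inter-observer variance as the shift plus this component, and the remaining residual as same-observer, between-day variance. State whether intra-individual variance includes observer disagreement. Base any interval for the observer shift on the participant-by-observer mean square, which has about 48 df when day is in the model.

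The cost is a short addition to the text and one more variance parameter, with no new data or participants. Intervals for the observer difference may be slightly wider.

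### The predictor regressions name no participant term, although each participant contributes four correlated areas; if the daily areas enter as separate rows, the PCS and HADS tests are too liberal

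*Protocol*

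**What the plan says.** All of this is in the protocol; no separate statistical analysis plan is at hand.

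- **Design.** Under General procedure: "The entire study consists of one screening day and four identical study days". Under Aim the cohort is 50 volunteers, and the first aim is to "Investigate the size of the area of secondary hyperalgesia following brief thermal sensitization on four different study days". A complete data set therefore holds 50 × 4 = 200 areas.
- **Predictors.** PCS and HADS are each completed once, before study day 1 (sections on the two questionnaires). HPDT and the two VAS measures from the long thermal stimulation are obtained on every study day.
- **Primary analysis.** Plan of statistical analysis specifies a variance component model that separates participant, experimental day and observer.
- **Secondary analyses.** The same section says that the ability of the five measures "to predict individual variations in areas of secondary hyperalgesia will be investigated by linear regression". Significance is to be judged by ANOVA methods, and prediction error is to be summarised with 95% prediction intervals, among other measures.
- **Data set and multiplicity.** "Analyses will be based on all observed data" stands between the definition of the intention-to-test population and the missing-data rule. Then: "A family wise error rate of 0.05 will be used and simultaneous assessment of multiple p-values will be subjected to single-step adjustment".
- **Expected variances.** The only figure is in Sample size estimation: "the ratio between the intra-individual variance and the inter-individual variance in secondary hyperalgesia may exceed 25" per cent.

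**The concern.** The authors recognise within-person correlation for the primary outcome, but the method named for predicting the same areas has nothing to absorb it: no participant effect, no participant mean, no cluster-robust standard error. Taken literally, linear regression with ANOVA tests assumes independent residuals, and four areas from one person are not independent. The study's own hypothesis of low intra-individual and high inter-individual variability is the situation in which that assumption fails most.

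PCS and HADS are hit hardest. They have 50 independent values, and repeating each on four rows adds little information while the nominal degrees of freedom rise from 48 to 198. The study could then report that catastrophizing or anxiety predicts hyperalgesia when it does not. The unit of analysis also decides what a 95% prediction interval covers: one person's area on one day, or a four-day mean.

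**Working it through.** **The plan's own figure.** The only stated figure to compare with is the family-wise error rate of 0.05. The protocol gives no power, effect size or intraclass correlation (ICC) for these regressions, so no sample size can be reproduced.

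**Inputs.**
- From the protocol: n = 50 participants, m = 4 areas each, and a within-to-between variance ratio r that may exceed 0.25.
- Assumed: two-sided tests; r varied from 0.25 to 2.0; ICC of the daily predictors varied from 0 to 1. PCS and HADS are constant over days, so their predictor ICC is 1.

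**Formulas**, for a regression that treats all rows as independent:
- ICC of the area = 1/(1 + r)
- Design effect DE = 1 + (m − 1) × ICC of area × ICC of predictor
- Actual type I error = 2 × [1 − Φ(1.96/√DE)]

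**PCS and HADS, unadjusted 5% test.** At r = 0.25: ICC = 1/1.25 = 0.80; DE = 1 + 3 × 0.80 = 3.4; √3.4 = 1.84, so the true standard error is 1.84 times the one reported; type I error = 2 × [1 − Φ(1.96/1.84)] = 0.288.

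| r | ICC of area | DE | Type I error | Simulated |
|---|---|---|---|---|
| 0.25 | 0.80 | 3.4 | 28.8% | 29.4% |
| 0.5 | 0.67 | 3.0 | 25.8% | 26.2% |
| 1.0 | 0.50 | 2.5 | 21.5% | 22.2% |
| 2.0 | 0.33 | 2.0 | 16.6% | not run |

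Each simulated figure comes from 10,000 runs of 50 participants × 4 days with no true association.

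**Daily predictors at r = 0.25.**
- Predictor ICC 0.7: DE = 1 + 3 × 0.80 × 0.7 = 2.68, error 23.1% (simulated 23.5%).
- Predictor ICC 0.5: DE = 2.2, error 18.6% (simulated 18.7%).
- Predictor ICC 0: DE = 1, error 5% (simulated 4.7%).

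**Does the single-step adjustment rescue it?** Bonferroni serves as an example, since the protocol names no specific method. With five tests each runs at 0.01, critical value 2.576. A pooled PCS or HADS test then has actual error 2 × [1 − Φ(2.576/√DE)]: 16.2% at r = 0.25 and 6.9% at r = 2.0. With ten tests (PCS total and three sub-scores, HADS total and two, HPDT and two VAS measures) the nominal level is 0.005 and the actual level at r = 0.25 is 12.8%. In each of these three cases one test alone exceeds the 5% meant for the whole family. At r = 2.0 with ten tests a single such test runs at 4.7% against its nominal 0.5%, which leaves almost nothing for the other nine.

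**After the fix.** Regressing the participant mean on the predictor, 50 rows, gave a simulated type I error of 5.2% (20,000 runs, r = 0.25), which is nominal within simulation error.

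**Prediction intervals.** On a scale where total single-day variance is 1, a four-day mean has variance ICC + (1 − ICC)/4. At r = 0.25 this is 0.80 + 0.05 = 0.85, so the standard deviation is √0.85 = 0.92 of the single-day value. At r = 2.0 it is 0.33 + 0.17 = 0.50, a factor of 0.71. An interval built on means is therefore too narrow for a single-day area.

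**The case against.** A reader might infer that the plan analyses 200 rows as independent and that its predictor tests run at 29%. The protocol does not support that.

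- It never gives a row count or says that rows are independent. The phrase about individual variations fits one value per participant, or a model with a participant effect, as well as it fits pooled rows. ANOVA methods can include a participant stratum.
- The sentence on using all observed data concerns the analysis set and missing values. It also covers the primary model, which does have a participant term, so it cannot be read as a choice of pooled rows.
- The 29% is an unadjusted, single-test figure for PCS and HADS at a ratio of exactly 0.25. The protocol says that the ratio may be higher, which lowers the error, and the figure does not carry over to the daily predictors.
- A family-wise error rate for the whole set of tests would need correlations among the predictors that the protocol does not give, so none is claimed here.
- These are secondary outcomes of a study that calls itself explorative, and details of a secondary model are often left to a statistical analysis plan.

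These objections stand as limits on the claim and on its size, but they do not remove the point. The protocol does not leave the method open: it names linear regression, next to a model with a participant term for the same areas. Nothing in it tells the analyst how to reduce four days to one value or how to handle the correlation. It also promises a family-wise rate that depends on valid p-values from each test.

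**Conclusion.** The concern holds in conditional form. The method named for the predictors makes no provision for four correlated areas per participant. If the daily areas enter it as separate rows, the unadjusted type I error for PCS and HADS is about 17% to 29%, for ratios from 2.0 down to 0.25. For HPDT, Max-VAS and VAS-AUC it lies between 5% and the PCS/HADS figure for the same ratio, depending on a predictor ICC that the protocol does not give. No ratio in the range examined brings PCS or HADS back to 5%, and single-step adjustment cannot correct p-values that are individually too small.

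The size rests on pooled rows, two-sided tests, complete data and a ratio in the stated range. The primary variance-component analysis is unaffected. The point should be fixed before analysis, but it does not threaten the main result.

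**What to change.** In Plan of statistical analysis, replace the linear regression by one of these:

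1. A linear mixed model for the daily area with a random participant intercept and fixed effects of day and observer, the predictor being tested against between-participant variation where it is constant over days; or
2. A linear regression of each participant's mean area on the predictor, with n = 50.

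State that the 95% prediction interval for a new person's single-day area is based on participant plus residual variance. If means are used, say that an interval taken directly from that regression covers a four-day mean. Apply the single-step adjustment to the p-values from the chosen model.

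For HPDT, Max-VAS and VAS-AUC, separate terms for the participant mean and the daily deviation would distinguish prediction between people from same-day variation. This is an option that depends on the question the sponsor wants answered, not a required correction.

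The cost is a few sentences and no new data. The downside is wider intervals for the predictor effects and probably fewer significant predictors.

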**Secondary outcomes**

To evaluate how precise the scores of PCS and HADS, total and sub-scores, predict the size of the area of secondary hyperalgesia following brief thermal sensitization.

To evaluate how precise HPDT and pain during 1 min. thermal stimulation of the skin (LTS) predict the size of the area of secondary hyperalgesia following brief thermal sensitization.

The results from this study are to be used in evaluating sample size in future studies.

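### The protocol fixes a single-step adjustment for the predictor p-values; the step-down version of the same procedure keeps the 0.05 family-wise error and can only add rejections

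*Protocol*

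**What the plan says.** The multiplicity rule is in the protocol, *Plan of statistical analysis*: "A family wise error rate of 0.05 will be used", and "simultaneous assessment of multiple p-values will be subjected to single-step adjustment". No specific procedure is named, so Bonferroni, Šidák and single-step max-T all fit the wording. No reason is given for choosing single-step.

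The same section describes one source of p-values: "Significance of the predictors will be assessed by Analysis of variance (ANOVA) methods". The regressions concern "the ability of PCS, HADS, HPDT, Max-VAS and VAS-AUC (following LTS), to predict individual variations in areas of secondary hyperalgesia". *Secondary outcomes* widens the set: "To evaluate how precise the scores of PCS and HADS, total and sub-scores, predict the size of the area".

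Besides significance, the plan reports "various summaries of prediction errors including 95% prediction intervals for the predictions". It asks for no simultaneous confidence intervals for the regression coefficients.

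**The concern.** A single-step method holds every p-value in the family to the same strict threshold, however many hypotheses have already been rejected. A step-down method starts at that threshold for the smallest p-value and relaxes after each rejection, because fewer hypotheses then remain that could be true nulls. Both control the family-wise error strongly at 0.05.

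The usual reason to stay with single-step is that it gives matching simultaneous confidence intervals. This plan does not use them, so the stricter rule brings no visible return. What is at stake is some power for the second and later predictors, in a study of 50 men whose sample size was aimed at variance components and not at these regressions.

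**Working it through.** **Inputs from the protocol**
- Family-wise error rate 0.05 (*Plan of statistical analysis*).
- Participants: 50 (*Study Design*).
- Family size: not stated. The analysis plan names 5 predictors. With the sub-scores in *Secondary outcomes* the count is PCS 1 + 3, HADS 1 + 2, HPDT, Max-VAS and VAS-AUC = 10.

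**Assumptions**, because the protocol gives no figures: correlation r between each real predictor and the area, a common correlation ρ between predictors (or between their test statistics), and the number of real predictors. Each predictor is tested separately.

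**1. The stated 0.05 under single-step adjustment.** For independent tests:
- Bonferroni: 1 − (1 − 0.01)^5 = 0.0490 for 5 tests; 1 − (1 − 0.005)^10 = 0.0489 for 10.
- Šidák, threshold 1 − 0.95^(1/m): 0.0500 for both.

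The plan's choice therefore does what it says.

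**2. Thresholds.** Holm compares the ordered p-values with 0.05/(m − j), j = 0, 1, …, and stops at the first failure.
- m = 5: 0.0100, 0.0125, 0.0167, 0.0250, 0.0500, against 0.0100 throughout for Bonferroni.
- m = 10: from 0.0050 up to 0.0500, against 0.0050 throughout.

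The first threshold is the same and no later one is stricter, so every single-step rejection is kept. Step-down max-T relates to single-step max-T in the same way.

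**3. Simulation with t-tests on correlations**, n = 50, 6,000 studies in each of 10 settings. Average power, single-step → step-down:

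| Tests | ρ | Real predictors | r | Bonferroni → Holm | max-T | At least one rejection (Bonferroni and Holm / both max-T) |
|---|---|---|---|---|---|---|
| 5 | 0 | 2 | 0.35 | 0.474 → 0.492 | 0.480 → 0.498 | 0.744 / 0.749 |
| 5 | 0.3 | 2 | 0.40 | 0.641 → 0.661 | 0.657 → 0.674 | 0.848 / 0.861 |
| 10 | 0.3 | 3 | 0.40 | 0.534 → 0.550 | 0.552 → 0.569 | 0.852 / 0.864 |
| 10 | 0.5 | 5 | 0.40 | 0.535 → 0.570 | 0.577 → 0.606 | 0.891 / 0.916 |
| 5 | 0.3 | 5 | 0.40 | 0.637 → 0.751 | 0.654 → 0.758 | 0.970 / 0.973 |
| 5 | 0.5 | 5 | 0.40 | 0.634 → 0.734 | 0.658 → 0.747 | 0.930 / 0.936 |
| 10 | 0.5 | 10 | 0.40 | 0.539 → 0.659 | 0.581 → 0.686 | 0.945 / 0.958 |

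The other three settings had no real predictor; there the error rate was identical for each single-step method and its step-down version (for example 0.045 and 0.045). In all 60,000 studies the step-down version never lost a rejection made by its single-step counterpart. Where true nulls existed, the step-down family-wise error was 0.035 to 0.052. The simulation standard error is √(0.05 × 0.95 / 6,000) = 0.003, so this agrees with 0.05.

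**4. What drives the gain.** Max-T, 10 z-tests with mean atanh(r)·√47, 20,000 studies per setting; gain in average power in percentage points:

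| r | ρ | 1 real | 2 real | 3 real | 5 real | 7 real |
|---|---|---|---|---|---|---|
| 0.30 | 0.3 | 0.0 | 0.3 | 0.7 | 1.8 | – |
| 0.45 | 0.3 | – | – | 1.6 | 3.6 | 6.0 |
| 0.45 | 0.8 | – | – | 0.8 | 1.7 | 2.9 |

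The gain grows with the number of real associations and, under max-T, roughly halves when the correlation rises from 0.3 to 0.8.

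**5. Crossing methods.** With 10 tests, ρ = 0.8, 3 real predictors and r = 0.45, average power was 0.789 for single-step max-T and 0.709 for Holm. Holm lost at least one max-T rejection in about 22% of studies.

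**The case against.** The strongest reply is that nothing here is wrong. Single-step adjustment controls the stated error rate, *Study Design* calls the study explorative, and the primary outcome (variance components) involves none of these tests. The secondary aim is how precisely the predictors predict, and the prediction errors and intervals that answer it do not depend on the adjustment. With few or weak real predictors the gain is close to nothing: at r = 0.30 with 3 real predictors the two max-T versions gave different rejections in only 2.5% of studies. All of this stands, and it limits the point to a minor one.

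A reader might infer three stronger things that do not hold.
- *That the plan inflates error or is invalid.* Step 1 of the working shows otherwise.
- *That any step-down method, Holm included, beats whatever was intended.* The guarantee is like for like. The protocol does not name its method, and if max-T was meant, a move to Holm can lose power (step 5).
- *That overlapping predictors, such as sub-scores of one scale or two summaries of one VAS curve, are where step-down gains most.* Under max-T, higher correlation shrinks the gain (step 4). What matters is how many associations are real.

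The reply does not supply a reason for single-step in this plan. The rule is fixed in the protocol, so an analysis plan that follows the protocol would inherit it.

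**Conclusion.** The point holds as a modest gain in efficiency. For any family of two or more tests, the step-down version of the intended procedure keeps strong control at 0.05 and rejects at least as much, whether the family is 5, 10 or split by secondary outcome.

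The size depends on assumed effects and correlations. Average power rises by about 0 to 6 points when some predictors are null and by up to about 12 when all are real (0.539 to 0.659 with ten tests under Bonferroni and Holm). The chance of at least one rejection is unchanged. Only the secondary outcomes are affected, and the change is desirable, not necessary.

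**What to change.** In *Plan of statistical analysis*, replace *single-step adjustment* with: *step-down adjustment (step-down max-T; or Holm if Bonferroni was the single-step method intended)*. Keep the family-wise error rate at 0.05. Make the change before the sealed questionnaires are opened and before any predictor p-value is computed.

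It needs no further participants, visits or type I error. The one loss is that step-down p-values have no simple matching simultaneous confidence intervals. If the investigators want such intervals, they should keep single-step and state that reason.
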